#### Procedure of secondary distribution of HIVST

All index participants will follow the one standard set of instructions and procedures for network-based online SD-HIVST regardless of group assignment. This procedure has been used in our previous studies and has shown effectiveness in increasing HIV testing coverage among Chinese MSM [24–26]. Ordering of HIVST kits and uploading test results will be all conducted using an online digital platform created and operated by a community health services center. Index participants can access this platform by following the public account of Xutong on WeChat, which is the largest social networking application in China.

Alters will be encouraged to perform all HIVST according to the manufacturers’ instructions using fingerstick blood samples. We will use SD Bioline HIV/Syphilis duo test kits (SD Bioline Company, South Korea). Each HIVST kit will have a delivery-tracking code, a result-tracking code, and a user guide manual attached to it. HIVST kits will be delivered to the destination address provided by applicants at request by post. The trained CBO staff verifies results based on photos uploaded by testers. Testers will be required to submit the testing evidence and test results by uploading photographs of their used kits to an online platform. That platform will be an anonymous system that testers can only access by scanning a QR code attached to their test kit box.

There will be two rounds for index participants to order HIVST kit(s) via the online platform. During the first three months, index participants can request at most five (5) HIVST kits based on their personal needs. They can personally use the kits or distribute them to others within their social network (hereafter, alters). In addition, index participants can order a personalized peer referral link, with which they can invite up to 5 unique alters to order one HIVST kit each. We will employ a refundable deposit strategy to reach a considerable response rate and facilitate linkage to care services. We will demand a refundable deposit amount of 40 RMB (≈ 7 USD) at each request. The deposit will be returned to the matched kit applicant through the same payment method within three business days after an uploaded testing result is verified by CBO staff.

All index participants will receive notification to order the second round of HIVST kits after completing the 3-month follow-up survey. Index participants who do not finish the 3-month follow-up survey will receive a survey reminder alongside the notice of the second round. For index participants who do not order any test kits during the first round, we will notify them about the second round when the first index participant completes the first follow-up survey. The only difference between the two rounds is that an index participant can be allowed to order up to 10 HIVST kits (5 HIVST kits in the first round) and can invite up to 10 unique alters (5 alters in the first round) to order one kit via the peer-referral link during the second round.

For results verification, trained CBO staff will first read test results according to uploaded photos. If a result is determined to be invalid, we will contact the tester via WeChat or phone call and ask whether the tester is willing to get re-tested. If a result is HIV-reactive or syphilis-reactive, the CBO staff will contact the teste to provide linkage to care and support services. The CBO staff will also verify the alters’ identification (by checking if the telephone number and WeChat ID provided by an alter are the same as the corresponding index participant). Only index participants that distribute HIVST to alters who use a different phone number and WeChat to upload test results will receive incentives. A fixed amount of 20 RMB (≈ 3 USD) will be offered to the corresponding index participant as a financial incentive once an alters’ test result is verified. Additionally, all testers will receive a fixed 20 RMB (≈ 3 USD) as encouragement and honorarium for their time used when a CBO staff validates their results for the first time.

### Outcomes

Our first primary outcome is to compare the average number of alters motivated by each index between two groups. The second primary outcome is to ascertain the mean number of newly-tested alters motivated by each index in each group in the same study period. Secondary outcomes will be 1) the mean number of tested alters motivated by each index in each group with HIV reactive results, and 2) evaluate the primary outcomes in subgroups categorized by age, sexual orientation, sexual intercourse history, residence, and previous HIV testing experience.

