### Hypothesis

We hypothesize that SHIs identified by the ensemble machine learning model will motivate more alters to test and identify more newly-tested alters (as first-time tested for HIV) through the SD-HIVST intervention than SHIs identified by the conventional scale.

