### Sample size

We use PASS version 16.0 to calculate a study sample size of 400 index participants (200 in each group), with an alpha of 0.05 and a loss to follow-up of 20%. Our estimated sample size can provide a power of 0.80 to detect differences between groups and are calculated based on the following assumptions.

#### Assumption 1

We assumed that SHIs identified by the model could motivate one more alter on average to get tested for HIV than SHIs identified by the scale, based on the results of our previous study [21].

#### Assumption 2

Based on the results of our previous study [25], we assumed that 40% of alters motivated by SHIs identified by the scale will be new testers. We also estimate that SHIs identified by the model can motivate 0.3 more newly-tested alters than SHIs identified by scale [22].

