#### Data analysis

We will use descriptive analysis to report baseline characteristics and use Shapiro-Wilk’s method for data normality test. If the data has a normal distribution, a two-sample t-test will be used to calculate a 95% confidence interval (CI) to compare the differences in outcomes between the two arms. We will use a bootstrapping method in calculating the 95% CI if the data distribution is not normal. Subgroup analysis will be used to evaluate the difference between the two groups in the different subsets of index participants. We will use R version 3.6.2 software for all the data analysis. The trial is registered with the Chinese Clinical Trial Registry (ChiCTR2000039632).

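### Two primary outcomes share one undivided alpha of 0.05 with no rule linking them: if either alone can carry the claim, the family-wise error is roughly 6–9%; if both are required, joint power can fall below 0.80

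*Protocol article*

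**What the plan says.** Four places in the protocol article bear on this.

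- **Outcomes.** "Our first primary outcome is to compare the average number of alters motivated by each index between two groups". The section then adds: "The second primary outcome is to ascertain the mean number of newly-tested alters motivated by each index in each group". The words first and second label the outcomes; no testing order is attached to them.
- **Sample size.** The calculation is made "with an alpha of 0.05 and a loss to follow-up of 20" percent, and the section concludes: "Our estimated sample size can provide a power of 0.80 to detect differences between groups". It gives two effect assumptions: a difference of 1 alter, and a difference of 0.3 newly-tested alters. It does not say whether 0.80 applies to each outcome, to at least one, or to both.
- **Data analysis.** If the data are normal, "a two-sample t-test will be used to calculate a 95% confidence interval (CI) to compare the differences in outcomes between the two arms". Otherwise: "We will use a bootstrapping method in calculating the 95% CI if the data distribution is not normal". The level is 95% either way, with no adjustment for two outcomes.
- **Hypothesis.** Model-identified influencers "will motivate more alters to test and identify more newly-tested alters". This is the nearest the article comes to a success rule, but it is worded as an expectation.

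**The concern.** Alpha and power have a definite meaning only once it is settled which result counts as success. The article fixes two primary outcomes, one alpha and the intervals, and leaves that step out. A reader following it could report either interval excluding zero as a positive primary result at 5%. That gives two chances of a false positive, so the stated 5% is not the error rate of the claim. If success on both was meant, the error is controlled, but the stated 0.80 need not be the power for that claim. Leaving the reading open also lets the claim be chosen after the results are known.

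**Working it through.** **Inputs from the article.** Alpha 0.05 (two-sidedness is inferred from the 95% intervals); power 0.80; 200 index participants per group with 20% loss, so 200 × 0.8 = 160 evaluable per group; differences of 1 and 0.3; 40% of alters being new testers (stated for the scale group only). The article gives no standard deviation (SD) and no correlation between the outcomes.

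**Step 1: the plan's own figure.** Without an SD, 400 can be neither reproduced nor refuted. The SD that would make 160 per group give 80% power at two-sided 0.05 is SD = difference / [(1.960 + 0.842) × √(2/160)]:

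- difference 1: 1 / 0.3132 = 3.19
- difference 0.3: 0.3 / 0.3132 = 0.96

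These SDs are back-solved, not documented. Both correspond to a standardised difference of 0.313.

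**Step 2: family-wise error if either outcome suffices.** With no true difference and test statistics correlated at ρ, the error is 1 − P(|Z1| < 1.96 and |Z2| < 1.96) under a bivariate normal. At ρ = 0 this is 1 − 0.95² = 9.75%, the largest value.

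| ρ | Family-wise error |
|---|---|
| 0 | 9.75% |
| 0.5 | 9.1% |
| 0.63 | 8.6% |
| 0.8 | 7.8% |
| 0.9 | 7.0% |
| 0.97 | 6.1% |
| 1 | 5.0% |

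**Step 3: a plausible ρ.** Newly-tested alters are a subset of all alters. As an assumption, let each alter be a new tester independently with probability 0.4. With mean μ and SD s for alters per index,

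ρ = 0.4s / √(0.24μ + 0.16s²).

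- Poisson counts (s² = μ): 0.4 / √0.40 = 0.63, error 8.6%, whatever the mean.
- μ = 2, s = 2: 0.8 / √(0.48 + 0.64) = 0.756, error 8.1%.
- μ = 1, s = 3: 1.2 / √(0.24 + 1.44) = 0.926, error 6.8%.

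Over assumed means of 0.5 to 3 and overdispersed SDs of 2 to 3.2, ρ runs from about 0.69 to 0.97 and the error from 8.4% down to 6.2%. With the Poisson case included, the range is roughly 6–9%.

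**Step 4: power if both are required.** If each outcome has power 0.80, joint power is 0.80² = 0.64 at ρ = 0, about 0.73 at ρ = 0.8 and about 0.77 at ρ = 0.97. If one outcome has 0.80 and the other 0.90 or 0.95, joint power at ρ = 0.8 is about 0.78 or 0.79.

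**Step 5: what splitting alpha would cost.** At 0.025 per outcome, with the back-solved SDs, 160 evaluable per group gives power of about 0.71 per outcome. Restoring 0.80 needs 2 × [(2.241 + 0.842) / 0.3132]² ≈ 194 evaluable, and 194 / 0.8 ≈ 243 enrolled per group, against 200 planned.

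**The case against.** **Scope.** A multiplicity rule is often left to the statistical analysis plan, one may exist, and a journal article condenses. That would answer a complaint about silence alone. Here the article itself commits to two primary outcomes, sizes the trial at an undivided 0.05 and states unadjusted intervals. A later document that split alpha would no longer match the stated sample size (step 5). The point stands as one about the design as stated.

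**The stronger reading.** A reader might infer that the false-positive rate is 7–8% in fact. The article does not support this. That figure needs either outcome alone to suffice, which is stated nowhere, and a correlation of about 0.77 to 0.90, which is not given. The Objectives and Hypothesis join the outcomes with *and*; if both must succeed, the error is at most 5%. This objection is right, and it is why the conclusion is conditional and the range wider.

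**Direction.** The hypothesis is directional. Counting only false claims in favour of machine learning, the either-outcome error at ρ = 0.8 is 3.9% against a nominal 2.5%. This is fair: the absolute rate is halved, but the inflation remains.

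**Joint power.** A reader might equally infer that requiring both outcomes makes the 0.80 wrong. That is not established. If 400 is the larger of two calculations, one outcome has power above 0.80 and the joint figure may be only slightly below it (step 4). The shortfall is possible, and its size is unknown.

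**Conclusion.** The point holds in conditional form. The article sets two primary outcomes against one alpha and one power and does not say which result is a success.

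- **Either suffices:** the two-sided family-wise error exceeds 5% at any correlation below 1. Roughly 6–9% is supportable, with a ceiling of 9.75%. The range rests on assumed means and SDs and on applying the 40% share to every alter.
- **Both required:** the error is at most 5%. Joint power can be below 0.80; the 0.73 assumes power of 0.80 for each outcome and a correlation of 0.8.

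The inflation is modest, and its direction under the either-outcome reading does not depend on the assumed figures. It should be corrected because the remedy costs almost nothing and, by the Trial status section, the statistical analysis had not begun.

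**What to change.** Before analysis, add a fixed sequence in the article's own order, keeping its outcome wording. For example: *The mean number of alters motivated per index will be compared first at two-sided 0.05. A difference in the mean number of newly-tested alters per index will be claimed, at two-sided 0.05, only if the first comparison is significant; otherwise it will be reported descriptively.*

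This holds the family-wise error at 5% or less, leaves power for the first outcome untouched and needs no more participants. The cost is that the second outcome can be claimed only after success on the first, so its power becomes the joint power (step 4). The Sample size section should say so and state which outcome the 0.80 refers to.

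Requiring both outcomes at 0.05 would also control the error and fits the Hypothesis wording, but the power would have to be restated as joint power. Splitting alpha is the costlier route because it reopens the sample size.

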### Participant timeline

We expect to start study recruitment from January 7, 2021, to January 22, 2021. Randomizing recruited participants into groups, identifying SHIs for each group, and notifying participants occurred in February 2021. The first round of HIVST orders starts from February 2021 to April 2021, and the second round of HIVST requests will be from June 2021 to July 2021. Follow-up surveys will be collected three months later following each ordering. The trial ends in October 2021.

### Sample size

We use PASS version 16.0 to calculate a study sample size of 400 index participants (200 in each group), with an alpha of 0.05 and a loss to follow-up of 20%. Our estimated sample size can provide a power of 0.80 to detect differences between groups and are calculated based on the following assumptions.

#### Assumption 1

We assumed that SHIs identified by the model could motivate one more alter on average to get tested for HIV than SHIs identified by the scale, based on the results of our previous study [21].

#### Assumption 2

Based on the results of our previous study [25], we assumed that 40% of alters motivated by SHIs identified by the scale will be new testers. We also estimate that SHIs identified by the model can motivate 0.3 more newly-tested alters than SHIs identified by scale [22].

### Recruitment

The recruitment banner ads will have a brief trial description and continue showing on Blued until a target population size of at least 2000 eligible MSM participants fills in the baseline survey. Each Blued user will only be able to finish the baseline survey once. After survey submission, eligible study participants will receive a random 8-digit verification code and the WeChat ID of SESH. All participants will be encouraged to add the SESH official WeChat and provide their unique 8-digit verified code to get 25 RMB (≈ 4 USD) as the time reimbursement of survey completion. We will add participants who do not add the SESH WeChat or send them reminder text messages according to their provided contact information in the survey. After identification, we will use Wechat or text messages to notify SHIs and ask for their verbal consent to participate in the SD-HIVST.

### Allocation and blinding

Study participants who are consented, meet inclusion criteria, and provide non-duplicate contact information (either cell-phone number or WeChat ID) will be randomly assigned to the scale group or the machine learning group by a computer-generated program with a 1:1 allocation. Only researchers will know the details of the group assignments, and study participants and CBO staff are blinded.

#### Data collection

All MSM participants will be required to complete an online survey during recruitment. Index participants will need to complete two to three surveys, including a baseline survey at their first ordering of HIVST kits, and one to two follow-up surveys based on the times of ordering. Alters will be asked to complete a survey when reporting their test results. All surveys are administered online and include electronic consent forms.

The baseline survey administered during recruitment will include questions from the following seven perspectives: sociodemographic, sexual intercourse history in the past three months, sexual health influencer scale [23], social network information, homoprejudiced violence scale [27], depression scale (patient health questionnaire-9) [28], and HIV and syphilis testing history.

The baseline survey of index participants includes additional questions from the following four perspectives: social network information, relationship with alters, experiences of secondary distribution, and social support scale [29, 30]. Questions of the survey administered to alters will include sociodemographic, sexual intercourse history in the past three months, the experience of receiving HIVST kits, previous HIV testing experience, and social network information.

#### Data management

In this trial, all surveys are self-completed, and data are stored electronically. The recruitment survey data are stored in WENJUANXING, a popular online survey tool in China. Data of index participants and alters are stored in JINSHUJU, a secure online platform where individuals can order HIVST kits, upload testing results, and fill in surveys. Only trained CBO staff and researchers will have access to JINSHUJU. We also assigned MSM participants pseudonyms following a pre-determined pattern when adding their WeChat.

#### Missing data plan

We will follow the intention-to-treat principle to conduct data analysis. Response to variables for primary and secondary outcomes analyses are required compulsory answers to complete the surveys. Therefore, we will not have any missing data in terms of analyzing the primary and secondary outcomes.

#### Data analysis

We will use descriptive analysis to report baseline characteristics and use Shapiro-Wilk’s method for data normality test. If the data has a normal distribution, a two-sample t-test will be used to calculate a 95% confidence interval (CI) to compare the differences in outcomes between the two arms. We will use a bootstrapping method in calculating the 95% CI if the data distribution is not normal. Subgroup analysis will be used to evaluate the difference between the two groups in the different subsets of index participants. We will use R version 3.6.2 software for all the data analysis. The trial is registered with the Chinese Clinical Trial Registry (ChiCTR2000039632).

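### A Shapiro-Wilk pre-test picks the interval method for small whole-number counts: the t-test branch is in effect unreachable at the planned size, and the rule can cost coverage only in small subgroups

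*Protocol article*

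**What the plan says.** The Data analysis section of the protocol article sets a two-stage rule. The analysts will "use Shapiro-Wilk’s method for data normality test". Then: "If the data has a normal distribution, a two-sample t-test will be used to calculate a 95% confidence interval (CI"). Otherwise: "We will use a bootstrapping method in calculating the 95% CI if the data distribution is not normal". The next sentence adds: "Subgroup analysis will be used to evaluate the difference between the two groups in the different subsets of index participants".

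The Outcomes section defines the two primary outcomes. The first is to "compare the average number of alters motivated by each index between two groups"; the second is "the mean number of newly-tested alters motivated by each index in each group". The number of HIV-reactive alters per index is a secondary outcome, and the primary outcomes are also to be examined in subgroups on five factors.

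The section on the procedure of secondary distribution bounds these counts. In round one an index may order five kits, and by referral link "they can invite up to 5 unique alters to order one HIVST kit each". In round two he may order ten kits and "can invite up to 10 unique alters (5 alters in the first round").

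**The concern.** Each outcome is a small non-negative integer per index participant. A normality test on such data mainly measures sample size: it rejects in large samples and often passes in small ones. Used as a switch, it has two possible effects. At full size, one of the two stated branches may never be used. In small subsets, the observed data may decide the method, so that neighbouring subgroups are analysed differently, and the fallback interval may be less well calibrated than the t interval it replaces. What is at stake is whether the reported 95% intervals cover at their stated level, and whether the method is really fixed before the data are seen.

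**Working it through.** **Inputs from the protocol article.** 200 index participants per arm, 20% loss, alpha 0.05, power 0.80; planned differences of 1 alter and 0.3 newly-tested alters (Sample size). Upper bound on alters per index: 5 + 5 + 10 + 10 = 30.

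**Not given, so assumed.** Control means, SDs, subgroup sizes, level of the Shapiro-Wilk test (0.05 used, per arm) and type of bootstrap.

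**The plan's own figure.** After loss, 200 × 0.8 = 160 per arm. With n = 2(1.960 + 0.842)² SD²/Δ² ≈ 15.70 SD²/Δ², 160 per arm follows if SD ≈ 3.19 for Δ = 1 (15.70 × 10.18 ≈ 160) or SD ≈ 0.957 for Δ = 0.3 (15.70 × 0.916/0.09 ≈ 160). No SD is stated, so N = 400 can be neither confirmed nor refuted. The implied SDs serve below as one plausible level of spread.

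**Step 1: is the t branch reached at full size?** Counts were simulated as Poisson or negative binomial, capped at 30, with 1,000 runs. The chance that a single arm passes Shapiro-Wilk at n = 160 or 200 was 0.000 for every mean from 0.4 to 5. It becomes appreciable only at much higher means: Poisson 10 gives 0.197 at n = 160, so both arms pass with probability about 0.197² ≈ 0.04; Poisson 15 gives 0.543, or about 0.29 for both.

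**Step 2: can the method differ between subgroups?** Chance that both arms pass:

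| n per arm | Poisson, 2 vs 3 | Neg. binomial, 2 vs 3, SD 3.19 |
|---|---|---|
| 10 | 0.57 | 0.08 |
| 15 | 0.44 | 0.007 |
| 20 | 0.27 | 0 |
| 30 | 0.04 | 0 |
| 40 | 0.001 | 0 |

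The single-arm results agree: for Poisson at n = 15, 0.578 × 0.772 ≈ 0.45. For newly-tested alters (0.4 vs 0.7, SD 0.957) the chance is 0.001 or less at every size. Switching is thus a feature of near-Poisson alter counts in small groups. If means are near 5 it extends to somewhat larger groups: a single Poisson arm passes with probability 0.588 at n = 40.

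**Step 3: how do the intervals cover?** Coverage of nominal 95% intervals, percentile bootstrap / t, from 1,500 runs (simulation error √(0.95 × 0.05/1500) ≈ 0.006):

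| n per arm | Poisson, 2 vs 3 | Neg. bin., 2 vs 3, SD 3.19 | Neg. bin., 0.4 vs 0.7, SD 0.957 |
|---|---|---|---|
| 10 | 0.921 / 0.951 | 0.903 / 0.956 | 0.891 / 0.957 |
| 20 | 0.919 / 0.937 | 0.919 / 0.955 | 0.917 / 0.953 |
| 40 | 0.943 / 0.949 | 0.937 / 0.961 | 0.937 / 0.956 |
| 80 | 0.948 / 0.954 | 0.937 / 0.952 | 0.935 / 0.949 |
| 160 | 0.943 / 0.945 | 0.945 / 0.948 | 0.939 / 0.943 |

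Much of the gap is one of width. The bootstrap standard error uses divisor n and a normal-type quantile, so its width relative to t is roughly √((n−1)/n) × 1.960/t. At n = 20 this is 0.975 × 1.960/2.024 ≈ 0.94, and the simulated ratio was 0.94. At n = 160 it is 0.997 × 1.960/1.967 ≈ 0.99, against a simulated 0.985.

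A further simulation with 2,000 runs per scenario gave, at 160 per arm, 0.938 to 0.948 for the percentile bootstrap and 0.944 to 0.954 for Welch. At 15 to 40 per arm it gave about 0.88 to 0.95 against 0.90 to 0.97, the Welch figure usually being 0.93 or higher.

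**Step 4: does the bootstrap type matter?** At n = 10, normal, basic and studentised bootstraps covered about 0.92 to 0.95, against 0.89 to 0.92 for the percentile interval. At n = 20 the studentised form (0.923 to 0.933) was only slightly better than the percentile form.

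**The case against.** The strongest reply is that nothing important is damaged. If the test always rejects at full size, the primary analysis is not chosen by the data at all: it is a bootstrap of the difference in means, at about one percentage point or less below the t interval in coverage. That stands. A reader might infer from the unused t branch that the primary intervals are too narrow or the primary conclusions unsafe; the documents and the figures above do not support that.

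Second, no subgroup sizes are stated. Halving 160 to 200 per arm on a two-level factor leaves 80 to 100, where the percentile interval still covered about 0.935 to 0.948. Nor does the Data analysis section say that the normality test is repeated within each subset. Both points stand, so the subgroup consequence is conditional.

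Third, the type of bootstrap is not named, and an article may leave that to the full protocol or analysis plan. This stands too. A reader might also infer that 5% subgroup comparisons really run at 7 to 8%. Simulated rates of that order were obtained with a percentile interval at 30 vs 30 and 40 vs 20, but the 8% comes from a single 40 vs 20 case (0.079 against 0.061 for Welch, 700 runs). The plan fixes neither those sizes nor that interval.

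Finally, frequent switching and marked overdispersion do not go together: with SD 3.19 both arms almost never pass from 15 per arm upwards. Switching and the larger coverage losses should therefore not be added together as though one set of assumptions produced both.

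What survives is the stated rule itself. It contributes nothing at full size and can only add instability or lose coverage in small groups.

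**Conclusion.** The point holds as a cheap improvement, not as a threat to the main result. For mean counts up to about 5, the Shapiro-Wilk step makes the t-test branch unreachable at 160 to 200 per arm. Means in that range are consistent with the planned differences of 1 and 0.3, although the article states no control mean. At means of 10 or more the branch is sometimes reached, so it would be wrong to call it impossible.

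The primary comparisons keep near-nominal coverage, about 0.94 to 0.95 with a percentile bootstrap. Any loss lies in subgroups of roughly 40 per arm or fewer, if such subgroups arise and the same rule is used in them: about 0.88 to 0.95 for the percentile interval at 15 to 40 per arm. In near-Poisson alter counts below about 30 per arm, the method may also change from one subgroup to the next. All these sizes depend on assumed means, dispersion, subgroup sizes and bootstrap type. Across the scenarios tabulated above, the fixed t interval covered as well as or better than the percentile fallback at every size.

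**What to change.** Delete the Shapiro-Wilk step and the choice that hangs on it. State one method in advance for all count outcomes and all subgroups: the difference between arms in mean count per index participant, with a Welch 95% confidence interval. The Trial status section says that statistical analysis has not begun, so on that account the change can still be made beforehand.

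The cost is one sentence in the analysis section and a line or two of R. N stays at 400 and no new data are needed. The downside is slightly wider intervals in small subgroups. At 20 per arm the percentile interval was 0.94 of the t width, so the fixed interval is about 6% wider (1/0.94 ≈ 1.06). A permutation p-value or a negative binomial ratio of means may be added as support, but neither is needed for the correction.

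### The subgroup analysis is described only as arm comparisons inside each subset, which cannot by themselves show that the effect differs between subsets

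*Protocol article*

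**What the plan says.** The Data analysis section of the protocol article gives the subgroup method in one sentence: "Subgroup analysis will be used to evaluate the difference between the two groups in the different subsets of index participants". The only comparative tools named in that section are a two-sample t-test and, for non-normal data, a bootstrap; either gives a 95% CI for the difference between arms.

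The Outcomes section makes this the second of two secondary outcomes: "evaluate the primary outcomes in subgroups categorized by age, sexual orientation, sexual intercourse history, residence, and previous HIV testing experience". There are two primary outcomes. The first: "Our first primary outcome is to compare the average number of alters motivated by each index between two groups". The second: "The second primary outcome is to ascertain the mean number of newly-tested alters motivated by each index in each group".

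The Sample size section gives "a study sample size of 400 index participants (200 in each group), with an alpha of 0.05 and a loss to follow-up of 20" per cent, and adds: "Our estimated sample size can provide a power of 0.80 to detect differences between groups". That power is for the overall comparison; none is given for subgroups.

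The article names no interaction or heterogeneity estimate, no adjustment for the number of subgroup comparisons and no exploratory label. The Hypothesis section concerns overall effects only.

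**The concern.** A subgroup analysis is usually meant to show whether the effect differs between kinds of participant. The quantity that answers this is the difference between subsets in the arm difference. The stated method instead estimates the arm difference separately in each subset. When one subset's interval excludes zero and the other's does not, the two effects may still be equal; the contrast depends largely on subset size and chance.

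At stake is any statement about the men for whom model-based identification outperforms the scale. The trial is sized for the overall comparison, so each subset is underpowered and mixed results are expected even under a uniform effect. The secondary-outcome rank gives these results more standing than an exploratory table would have.

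**Working it through.** **Inputs from the protocol article**
- 200 index participants per arm with 20% loss: 200 × 0.8 = 160 evaluable per arm (Sample size).
- Alpha 0.05, sidedness not stated; power 0.80 (Sample size).
- Differences to detect: 1 alter and 0.3 newly-tested alters (Sample size).
- Five factors and two primary outcomes (Outcomes).

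**Assumptions**
- Two-sided test, two levels per factor, no adjustment, and 80% power for each outcome. The number of levels is not given; more levels would add comparisons.

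**Step 1. The plan's own sample size.** It cannot be reproduced, because no SD is stated. Solving SD = δ / [(1.96 + 0.84) × √(2/160)] gives about 3.19 for δ = 1 and about 0.96 for δ = 0.3. Steps 2 to 4 do not need the SD, since they start from the stated power.

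**Step 2. Same effect in everyone, equal halves.**
- Overall non-centrality: 1.96 + 0.84 = 2.80.
- In each half: 2.80/√2 = 1.98.
- Power in each half: Φ(1.98 − 1.96) = 0.508, about 51%.
- One half significant and the other not: 2 × 0.508 × 0.492 = 0.50.

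If alpha were one-sided, the non-centrality per half would be (1.645 + 0.842)/√2 = 1.76, power Φ(0.11) = 0.545 and discordance 2 × 0.545 × 0.455 = 0.50, so sidedness makes little difference.

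**Step 3. A 25/75 split.** Power is Φ(2.80 × √0.25 − 1.96) = 0.288 in the smaller subset and Φ(2.80 × √0.75 − 1.96) = 0.679 in the larger. Discordance is 0.288 × 0.321 + 0.679 × 0.712 = 0.58.

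**Step 4. The interaction test.** With no true effect modification it rejects at its nominal rate. Simulated rates were 4.9% (50/50) and 5.8% (25/75).

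**Step 5. Across the whole trial.** The number of comparisons is 5 factors × 2 levels × 2 outcomes = 20.

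| Situation | Result | Basis |
|---|---|---|
| No effect: expected false positives | 20 × 0.05 = 1 | arithmetic |
| No effect: at least one of 20 significant | 1 − 0.95^20 = 64% | if independent |
| No effect: at least one of 20 significant | 38% | simulation, overdispersed counts |
| No effect: at least one of 20 significant | 42-50% | simulation, normal outcomes, correlation 0.8 to 0 |
| Uniform effect: discordant pairs out of 10 | about 5 | simulation, normal outcomes |
| Uniform effect: at least one discordant pair | 90-97% | both simulations |
| No effect modification: at least one of ten unadjusted interaction tests significant | 34-41% | simulation, normal outcomes |

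The simulated rates fall below 64% because the same participants enter the subsets of every factor and both outcomes.

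**Step 6. Power of the interaction test.** With equal halves, the standard error of the difference between two subset effects is twice that of the overall effect. An interaction as large as the overall effect therefore has non-centrality 2.80/2 = 1.40 and power Φ(1.40 − 1.96) = 0.29.

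**The case against.** The strongest objection is that the article contains no rule for interpreting subgroups. A reader might infer that a difference significant in one subset and not in another will be taken as effect modification, or that the results will be used to say for whom the model works. The documents do not support that: they hypothesise no effect modification, never propose comparing significance across subsets, and frame the arm comparison as a 95% CI. This part of the objection stands.

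It can also be said that interaction tests, multiplicity and cut-points are commonly left to an analysis plan, which is not shown, and that reporting subset estimates with CIs is ordinary practice. Absence alone would indeed be no finding. But the article does state a target, the arm difference inside each subset, and ranks it as a secondary outcome. If a fuller plan estimates interactions, it answers a different question from this sentence, which would still need rewording.

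The trial-wide figures do rest on assumptions. Factor levels, subset sizes and count distributions are not given. The overdispersed-count simulation used means of 1 and 2 alters with 40% of alters new testers; if the 40% applies to both arms, that is 0.4 against 0.8, a difference of 0.4 where the plan assumes 0.3. Nor is one sample size likely to give exactly 80% power for both outcomes. Those figures should therefore be read as ranges. The 50% per pair needs only the stated power, equal halves and a uniform effect.

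Finally, an interaction test does not remove multiplicity: ten unadjusted tests still give 34-41%. The fair trial-wide contrast under a uniform effect is 90-97% against that, not against 5%. Naming the five factors in advance is also a real safeguard.

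**Conclusion.** The point holds in a limited form. The subgroup method, as described, cannot by itself show that the effect differs between subsets. Under the Step 2 assumptions it yields a misleading contrast in about half of factor-outcome pairs, against about 5% for an interaction test. With no effect, some subset comparison is significant in roughly 38-50% of trials.

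This concerns the clarity of a secondary analysis. The primary outcomes and their analyses are untouched, and the article does not commit the investigators to a wrong reading of the subsets. It is worth correcting because the method is stated, the analysis ranks as a secondary outcome and the remedy is cheap.

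**What to change.** In Data analysis, replace the subgroup sentence with wording such as: *For each of the five factors and each primary outcome, any difference between subsets will be judged by the arm-by-factor interaction estimate with its 95% CI, on all index participants. Factor values come from the recruitment survey completed before randomisation. Subset estimates with CIs are descriptive. The ten interaction results are exploratory; if any claim of effect modification is made, they will be Holm-adjusted.* Align the second secondary outcome in Outcomes with this. A factor with more than two levels would need one joint interaction test to keep the count at ten.

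The cost is wording in two sections and a few lines of R. No new data appear to be needed: Data collection lists sociodemographics, sexual history and HIV testing history in the recruitment survey, although it does not itemise age, sexual orientation or residence. Trial status says the statistical analysis had not begun. The drawback is low power, about 29% for an interaction as large as the overall effect and less after Holm, so few subgroup claims will be possible.
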